### **2.1 Quantitative studies**

#### **2.1.1 Acute respiratory infection (ARI) hospitalisation data and family costs**

**2.1.1.1 Secondary research question:** Is there reduced hospitalisation from ARI (during the last episode) in the intervention compared to control arms?

**2.1.1.2 Outcomes:** Hospitalisation during the last episode of ARI (cough with difficulty breathing) as reported by the mother. ARI hospitalisation has been added because of the

finding of a 30% reduction in self-reported ARI at 6 months post-intervention plus a statistically significant reduction in hospitalisation for diarrhoea. If the hygiene practices are continued at high rates, hospitalisation for ARI may also be reduced at 2 years.

**Methods:** One question is added about the hospitalisation of the child during its last ARI episode defined in the same way as in the 6-month follow-up.

### **2.1.1.3 Additional ARI health economic analysis of 2 years data**

If the intervention is effective in reducing the presence of infant respiratory diseases as was shown at 6 months, there are likely to be important economic implications.

**Methods:** The methods and questions in the structured questionnaire tool will be similar to the diarrhoea health economic analysis component described in the 6-month analysis. Only the questionnaire has had components added about child's ARI costs (cost to the family) and these questions are similar to those for diarrhoea that were tested and had received ethical approval.

## **2.1.2 Adult/family-food handling/preparation hygiene practices, coliform growth of family-food samples, diarrhoea in mother as secondary outcome**

**2.1.2.1 Secondary research question:** Has the weaning-food hygiene community intervention improved safety and hygienic preparation and handling of family-food by the mother and the rate of diarrhoea of the mother?

### **2.1.2.2 Family-food Outcomes (similar to weaning-food outcomes):**

(1) The observed mean proportion of **all five key food-related behaviours** as a fraction of all opportunities for performing the behaviours during the observation period (6am–3pm by

female data collectors) (Table 1; practices 1-5 and not including boiling water since water is often boiled for tea anyway; hereafter called *5-behaviours*).

(2) The observed mean proportion of **each of the individual five** key food-related behaviours (Table 1; practices 1-5 and including boiling water since water is often boiled for tea anyway) as a fraction of all opportunities for performing each behaviour during the observation period (6am–3pm by female data collectors) (hereafter called *5-behaviours*).

(3) Any days of diarrhoea (three watery stools in 24 hours) over the past seven days reported by the mother for the mother herself.

Our 6-month follow-up evaluation design which is to be repeated at 2 years included observing the cooking of the family breakfast and lunch and taking samples of the family-food at breakfast and at lunch (as well as the weaning-food samples and water). This was used to mask the data collectors observing the mothers' weaning-food hygiene practices and masking the mothers since our intervention messages were only about weaning-food and family food data were not monitored rigorously nor analysed.

In the 2-year follow-up this exploratory data will be quality checked and analysis has been added to our outcomes, since preliminary data from our pilot village indicate that after 2 years post intervention, the villagers apply the behaviours and for some of the families this has influenced the way mothers prepare the food for the whole family. Given the likelihood of an improvement in family-food hygiene practices at 2-year follow-up, we intend to analyse the adult/family-food related behaviours during cooking and food handling observations of family meals at 2-year follow-up.

**Methods:** Only the question about mother's diarrhoea is added in the first page of the questionnaire for the 2 years tools since the consent form, and observations, from the 6-month follow-up already contained family-food components.

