### **1.2.3 Outcome data collection**

Evaluation of outcomes took place six months after the last of the four day village visits during the high-risk rainy season. We hypothesised that if families were to retain the weaning-food practices learnt six months earlier, during this busy and high-risk period of the year, then our intervention would be successful. Independent newly recruited female data collectors received training for data collection. They moved in a group visiting one village per day and for each village one data collector was assigned to a mother who they observed for the day from approximately 6am-3pm.

An observation checklist was designed to collect data on mothers' food hygiene practices. As the baby food is made at the same time as family breakfast, the practices were those for preparing morning's food. Questionnaires were piloted and were used to collect data on the background characteristics of each family, the mother and child, data on income, health education related knowledge, the incidence of diarrhoea, ARI and hospitalisation for the index child, plus other questions that acted as diversions.

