### **1.2.5 Outcomes and outcome measures**

The primary outcome was the observed difference between the arms in the mean proportion of all five key food-related behaviours (Table 1) versus all opportunities for performing the behaviours during the observation period (6am–3pm by female data collectors) (hereafter called *5-behaviours*). The other outcomes were:

- (1) Microbial (total coliform) growth from weaning-food after making and after storage, and from water, before being consumed by the infant.
- (2) Presence of any days of diarrhoea (three watery stools in 24 hours) over the past seven days reported by the mother.
- (3) Presence of any days of ARI (cough with difficulty breathing) over the past seven days reported by the mother.
- (4) Reported hospital admission as the result of the last diarrhoea episode.
- (5) The mean proportion of each individual food hygiene practices (including boiling water behaviour not a part of food hygiene behaviours) versus all opportunities for performing each behaviour during the observation period (6am–3pm).

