### **1.2.6 Sample size**

Observations during the formative research indicated that the population proportion of events in which correct behaviour was displayed (i.e. practices of heating of stored food, hand washing with soap before food preparation, during food preparation if contaminated, and before feeding the baby (measured in the first time activity occurred)) was 17/150 (11.3%). For the sample size calculation, we assumed an intra-cluster correlation coefficient (ICC) of 0.04 between villages and a coefficient variation of cluster size 0.22. We aimed to detect a minimum of a 25% absolute increase in behaviour in the intervention compared to the control arm. Thus with a significance level of 5% and 95% power, 15 clusters per arm, with a

minimum of 12 mothers per cluster was needed. Assuming loss to follow-up we intended to recruit 20 mothers within each village. In a sensitivity analysis, assuming a larger ICC of 0.1, the power (84%) remained reasonable.

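### The family-food composite includes a breakfast made alongside the weaning food, so a pooled positive result cannot by itself show carry-over to food cooked for the family alone

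*Protocol*

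**What the plan says.** Protocol section 1.2.5 defines the primary outcome as the mean proportion of the five key Table 1 behaviours "versus all opportunities for performing the behaviours during the observation period", 6am to 3pm, and calls it *5-behaviours*. That wording does not restrict opportunities by type of food. Section 1.2.3 describes what is observed: "As the baby food is made at the same time as family breakfast, the practices were those for preparing" the food of the morning.

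Section 2.1.2.1 adds a question for the 2-year follow-up: whether the programme has "improved safety and hygienic preparation and handling of family-food by the mother". Section 2.1.2.2 answers it with Table 1 practices 1 to 5, expressed "as a fraction of all opportunities for performing the behaviours during the observation period", again 6am to 3pm, again by the female data collectors and again labelled *5-behaviours*. The design to be repeated "included observing the cooking of the family breakfast and lunch and taking samples of the family-food at breakfast and at lunch". The stated intention is: "we intend to analyse the adult/family-food related behaviours during cooking and food handling observations of family meals at 2-year follow-up".

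The reason given for adding the outcome is that pilot-village data suggest the behaviours have lasted and that "for some of the families this has influenced the way mothers prepare the food for the whole family". The same section says that the intervention messages concerned weaning food only.

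**The concern.** The reason for the new outcome is a carry-over claim: a campaign about weaning food has changed how mothers cook for everyone. To test that claim, the family-food measure needs events that are not also weaning-food events. At breakfast the two may coincide. A mother who washes her hands and pots before a joint preparation does so for both foods at once, and the definitions in 1.2.5 and 2.1.2.2 would admit that act to both composites.

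A persisting effect on weaning-food behaviour would then raise the family-food score even if the mother changed nothing when cooking for the family alone. What is at stake is how one added secondary outcome is read. The shared label makes it easier to report one effect as two separate findings.

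**Working it through.** The protocol states no figure for the family-food outcome, so there is none to reproduce. The check compares the definitions and then illustrates the possible size.

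**Definitions side by side**

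| | Primary (1.2.5, 1.2.3) | Family food (2.1.2.2) |
|---|---|---|
| Practices | Table 1, five food practices | Table 1, practices 1–5 |
| Window | 6am–3pm | 6am–3pm |
| Observers | female data collectors | female data collectors |
| Label | *5-behaviours* | *5-behaviours* |
| Meals | morning preparation (1.2.3); all opportunities in the window (1.2.5) | family breakfast and lunch |

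**Where overlap can arise.** Three of the five practices belong to preparation and cooking: hand-washing before preparation, utensil washing, and hand-washing when contaminated during cooking. At a joint breakfast these may serve both foods. Reheating stored food and hand-washing before feeding the child are not obviously shared, and nor is lunch preparation. The overlap is therefore partial.

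**Is there an attribution rule?** None appears in the protocol. Section 2.1.5 refers back to the 6-month analysis, but 2.1.2.2 says the family-food data were not analysed then.

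**Illustration of size.** Inputs:
- Control rate 11.3% (1.2.6, 17/150), assumed for shared and non-shared events alike.
- Effect on shared events +25 points (1.2.6, the minimum increase the trial aimed to detect), giving 36.3%.
- Effect on all non-shared events: zero (assumption, meaning no carry-over).
- Share *s* of family-food opportunities that are shared: not in the protocol; assumed 25% to 75%.

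Apparent ratio = [*s* × 0.363 + (1 − *s*) × 0.113] / 0.113 = 1 + *s* × 0.25/0.113.

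- *s* = 0.25: 0.1755/0.113 = 1.55 (difference 6.3 points)
- *s* = 0.50: 0.238/0.113 = 2.11 (12.5 points)
- *s* = 0.75: 0.3005/0.113 = 2.66 (18.8 points)

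If opportunities were spread equally over five practices and two meals, with three practices shared at breakfast only, *s* = 3/10 and the ratio is 1 + 0.30 × 0.25/0.113 = 1.66.

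If only half the planning effect (12.5 points) persisted at 2 years, the ratios at 25%, 50% and 75% would be 1 + *s* × 0.125/0.113 = 1.28, 1.55 and 1.83.

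**Rough chance of p < 0.05 with no carry-over.** This assumes 15 clusters per arm, 26 mothers per cluster, a cluster-size coefficient of variation of 0.22 and the full 25-point effect on shared events.

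Design effect = 1 + [(1 + 0.22²) × 26 − 1] × ICC, which is 2.05 at ICC 0.04 and 3.63 at ICC 0.1. The effective number per arm is 390/2.05 ≈ 190 or 390/3.63 ≈ 107. A two-sided 5% comparison of two proportions then gives, for *s* = 25%, 50% and 75%:
- ICC 0.04: 41%, 90% and 99.6%
- ICC 0.1: 26%, 68% and 93%

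This treats each mother as one yes/no observation, whereas the planned model is a Poisson model with an offset for opportunities. It is an order of magnitude only.

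**The case against.** **Double scoring is not stated.** A reader might infer that the same breakfast events are definitely counted twice. The protocol does not say so. Being made at the same time need not mean the same pot or the same scored act. Section 2.1.2.2 treats family-food samples as additional to weaning-food samples, and says the 6-month observations already had family-food components. Sections 1.2.10 and 2.1.4 describe weaning-food items embedded in a larger observation package. The checklist is not shown, and an attribution rule may sit there or in the SAP. This stands, so the claim is limited to *may count*. Separate forms would not fully remove the issue, because one hand-wash before a joint preparation is still one act.

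**A cleaner joint breakfast is a real family-food improvement.** Section 2.1.2.1 asks only whether family-food preparation improved, and it pairs this with the mother's own diarrhoea, for which breakfast hygiene is relevant. This also stands. A reader might conclude that the pooled outcome is invalid, or that its true value is a ratio of 1.0. The documents do not support that. The pooled outcome answers 2.1.2.1 and fails only for the carry-over reading in the rationale of 2.1.2.2.

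**Lunch is not stated to be family-only.** Section 2.1.3 says the older children eat some family food, and 1.2.4 has stored weaning food fed after at least three hours, which can fall within the observation window. Replacing the composite with lunch alone would rest on an unsupported premise and would discard a real family meal. This stands.

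**The illustration is hypothetical.** The shared fraction is assumed. The 11.3% baseline excludes utensil washing and includes reheating and washing before feeding. The 25 points is a 6-month design value, not a residual effect at 2 years. All of this is correct. The figures show direction and plausible scale and are not estimates.

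**Conclusion.** The point holds in a limited form. As defined, the pooled family-food composite may share breakfast preparation events with the primary outcome. A positive result would therefore be evidence of a cleaner joint breakfast, but not by itself evidence that the behaviours carried over to food cooked for the family alone.

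The overlap cannot be sized from the protocol. The ratios of 1.55 to 2.66 depend on 25% to 75% of opportunities being shared, the full 25-point effect persisting, equal control rates across events and no change elsewhere. Under an equal spread of opportunities the ratio is 1.66, and smaller residual effects shrink all of these figures.

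Severity is low. The outcome is secondary, the data are described as exploratory, and neither the primary outcome nor its analysis is affected.

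**What to change.** In section 2.1.2.2:

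1. Keep the pooled family-food composite, but give it a label distinct from *5-behaviours*.
2. Pre-specify that the composite and the individual family-food behaviours are also reported in two parts: (a) preparation events shared with weaning food, mainly breakfast; and (b) events that do not produce weaning food, mainly lunch where the records confirm this.
3. State that any conclusion about carry-over to family food rests on (b).

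If the observation form or the SAP already says how joint breakfast events are attributed, cite that rule here.

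The cost is a few sentences and a split in the analysis. Lunch is already observed, so no new fieldwork is apparent, provided the records identify the meal. The downside is fewer opportunities and a wider interval for (b).

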### **2.1.3 The population sample of mothers per village for 2 years evaluation data**

**(including additional variables in 2.1.1 and 2.1.2)**

We aim to select mothers who are currently weaning or have children who may have a combination of weaning and family food (E.g. 24-36month old children). As such some will be those who would not have been pregnant or had an infant at the time of the 4-days campaign visits or the 5th-month reminder.

For sampling frame, as with the 6-month follow-up the baseline list of children in the villages will be updated using the maternal-child health register and village health worker's list of children in each village. From these there will be 26 mothers chosen from each of the control and intervention villages. Sample size will be 23-26 mothers per cluster (as suppose to the target of 20 at the 6-month follow-up) because as indicated in the 6-month sample size calculation a minimum of 12 mothers per cluster of weaning children is needed (see above sample size for 6-month follow-up) but at 2 years we have 2 groups of mothers: new mothers and those who are mothers at the time of the 4-days campaign activities. (New mothers at 2-year follow-up are those with children 6-25month who will be eating weaning-food. Children aged 26-36 months will still, for the most part, be eating weaning-food at 2-year follow-up plus some of the family-food. Their mothers would have been pregnant during the 4-days campaign visits of the intervention in December to February 2014 and ready to wean at the 5th-month reminder visit. This population are the candidates most likely to *remember and practice* the hygienic behaviours while still *making* weaning-food during the 2-year assessment.) Therefore, we aim to have approximately 12 of each sub-group of mothers recruited. All individual mothers or main carers of children 6 to 36 months living in the village for a minimum of 2 years will be eligible for selection but mothers who are not available for cooking the child's weaning-food during the 2-year evaluation visit will be

excluded. (All mothers were available for the 6-month evaluation survey so we envisage very few or no mothers will be excluded).

To capture all these sub-groups of mothers, the selection of the mothers will be stratified as follows:

1. All mothers of children age 18 to 24 months will be chosen.
2. The rest of the mothers will be chosen according to the following formula:
$$x = \frac{(26 - \text{all mothers with 18 to 24 month old children})}{2}$$
3. Then,  $x$  number of mothers with children aged 6-18 months and  $x$  number of mothers with children aged 24-36 months will be randomly chosen from the list.

For sub-group analysis, ‘New mothers’ will be classified as those with children 6-25m since these mothers would not have had a child at before the 5th village reminder visit and the 6-month evaluation and so as mothers were not a part of the MaaChampion program when any part of the intervention was taking place in the villages.

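### The two-year selection rule does not deliver the stated target of about 12 mothers in each sub-group per village; the 26–36-month group would be expected to get about 7–9

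*Protocol*

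**What the plan says.** All of this is in section 2.1.3 of the protocol.

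- **Total.** "Sample size will be 23-26 mothers per cluster". The reason given is that the six-month calculation needs at least 12 mothers per village and that two groups of mothers now have to be covered.
- **Groups.** "New mothers at 2-year follow-up are those with children 6-25month who will be eating weaning-food". The second group is described thus: "Children aged 26-36 months will still, for the most part, be eating weaning-food at 2-year follow-up plus some of the family-food". The sub-group definition at the end of the section repeats 6–25 months for new mothers.
- **Target.** "Therefore, we aim to have approximately 12 of each sub-group of mothers recruited".
- **Selection, step 1.** "All mothers of children age 18 to 24 months will be chosen".
- **Selection, steps 2 and 3.** With m the number taken in step 1, x = (26 − m)/2. The rule then draws x "number of mothers with children aged 6-18 months and" the same "number of mothers with children aged 24-36 months will be randomly chosen from the list".

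Section 2.1.5 names one sub-group analysis, the effect in new mothers.

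**The concern.** The sampling bands are cut at 18 and 24 months, but the analysis groups are cut between 25 and 26 months. Two of the three bands lie wholly in the new-mother group, and so does the start of the third. The older group can be filled only from part of the third band, and every mother taken in step 1 reduces the places left in that band. The rule therefore favours new mothers whatever the village looks like.

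About 12 per group is the only reason the section gives for enlarging the sample from 20 to 23–26. If the rule does not give that split, the stated per-group size is wrong. The group left short is the one the section regards as most likely to have retained the taught practices.

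**Working it through.** **Inputs from the protocol.** Total of 26 per village (23–26), target of about 12 per group, group and band limits: section 2.1.3. Villages of 200–450 people, and 41,334 under-fives among 201,506 people = 20.5%: section 1.2.1. Baseline 17/150 = 11.3%, absolute increase of 25 points, ICC 0.04, coefficient of variation 0.22, 15 villages per arm: section 1.2.6.

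**Assumptions not in the protocol.** Ages spread evenly over the 60 months under five; one eligible mother per child; no loss from the residence and availability criteria.

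**1. The stated figure.** An equal split gives 23/2 = 11.5 to 26/2 = 13, which is about 12 of each. The target is what an equal split would give, but the rule does not split equally.

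**2. Bounds that need no age assumption.** Let O be the older group and N the new mothers.
- O ≤ x = (26 − m)/2, so O ≥ 12 requires m ≤ 2. At m = 3, x = 11.5; from m = 4, x is 11 or less however it is rounded.
- N = m + x + (x − O), so N − O = m + 2(x − O) ≥ m. The groups are equal only if m = 0 and no child of 24–25 months is drawn.

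**3. Expected split for a full 26.** The 24–36-month band is 12 months wide, and 10 of those months belong to the older group. Hence O = x × 10/12 and N = 26 − O.

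| m | x | O | N |
|---|---|---|---|
| 0 | 13.0 | 10.8 | 15.2 |
| 2 | 12.0 | 10.0 | 16.0 |
| 3 | 11.5 | 9.6 | 16.4 |
| 4 | 11.0 | 9.2 | 16.8 |
| 6 | 10.0 | 8.3 | 17.7 |
| 9 | 8.5 | 7.1 | 18.9 |

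Counting months inclusively (11/13 in place of 10/12) changes O by at most 0.2. With 23 in the formula and m = 4–9, O is 7.9–5.8 and N is 15.1–17.2.

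**4. By village size.** Children per month of age = 0.205 × population/60, and m is six times that. Draws are capped at the children available.

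| Population | m | x | Children 24–36 m | O under the rule | N under the rule | Children 26–36 m |
|---|---|---|---|---|---|---|
| 200 | 4.1 | 10.9 | 8.2 | 6.8 | 13.7 | 6.8 |
| 250 | 5.1 | 10.4 | 10.3 | 8.5 | 17.1 | 8.5 |
| 300 | 6.2 | 9.9 | 12.3 | 8.3 | 17.7 | 10.3 |
| 350 | 7.2 | 9.4 | 14.4 | 7.8 | 18.2 | 12.0 |
| 400 | 8.2 | 8.9 | 16.4 | 7.4 | 18.6 | 13.7 |
| 450 | 9.2 | 8.4 | 18.5 | 7.0 | 19.0 | 15.4 |

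Up to about 250 people the rule already takes every available child aged 24–36 months. About 350 people are needed before 12 children aged 26–36 months exist at all.

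**5. Loss due to the rule.** Averaged evenly over 200–450 people, O is 7.8 under the rule. Taking all available children aged 26–36 months, up to 12, would give 10.4. The loss is 1 − 7.8/10.4 = 25%, or about 117 against 157 mothers per arm (15 villages).

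**6. Power.** The design effect for n mothers per village is 1 + ((1 + 0.22²)n − 1) × ICC.
- n = 12, ICC 0.04: design effect 1.463, effective 180/1.463 = 123.0 per arm, power 99.7% for 11.3% against 36.3%. The protocol states 95%, which I do not reproduce.
- n = 7, ICC 0.04: design effect 1.254, effective 105/1.254 = 83.8 per arm, power about 97%.
- ICC 0.1: about 97% at n = 12 and 92% at n = 7. The protocol states 84% in its sensitivity analysis at that ICC.

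**The case against.** The strongest defence is that the text states an approximate aim, that the planned analyses do not depend on it, and that small villages could not supply 12 older-group mothers under any rule. Much of this stands, and it rules out several stronger readings.

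- **That 12 is out of reach in every village.** This does not follow. With m = 0, x is 13, and the chance that at least 12 of the 13 drawn are aged 26 months or more is about 34% under even ages; with m = 2 it is about 11%. If step 1 is read as already taking the 24-month-olds, the expected number at m = 0 is 13 × 11/12 = 11.9. The bound is strict only from m = 3 upwards.
- **That the older group falls short of 12 × 15 = 180 per arm because of the rule.** Villages below about 350 people would not have 12 such children, so 180 is not a fair benchmark. In the smallest villages the rule loses none, and the new-mother count near 14 there reflects fewer than 26 eligible children, not the formula.
- **That the trial loses power.** The named sub-group analysis concerns new mothers, who exceed 12, and the main comparison uses all sampled mothers. No separate analysis of the 26–36-month group is specified.
- **That the overlap at 18 and 24 months leaves children unallocated.** Step 1 comes first and the later steps concern the remaining mothers, so the order can settle the boundary ages.

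What the defence does not remove is the mismatch between the target and the rule. In villages of about 300 people or more there are more older-group children than the rule takes, and the expected number is about 7–8.

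**Conclusion.** The concern holds as a wrong stated per-group size. The selection rule does not match the analysis groups and does not deliver about 12 of each. That the older group cannot reach 12 when m is 3 or more, and that new mothers outnumber it by at least m, follows from the rule alone.

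The expected 7–9 older-group mothers and 17–19 new mothers (about 14 in the smallest villages) rest on even ages under five and one eligible mother per child, neither of which the protocol gives. Under the same assumptions the rule accounts for a loss of roughly 25% of the attainable older group; the rest of the distance to 12 is availability.

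A reader might infer an underpowered trial or sub-group analysis. The protocol does not support that: the group it plans to analyse is the over-filled one, and under its stated main inputs even 7 per village gives about 97%. Because I do not reproduce its own power figures, the safe statement is that no loss below the stated 95% is shown. The point needs correcting, but it does not threaten the main comparison.

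**What to change.** In section 2.1.3, replace the target of about 12 per group with the numbers the rule is expected to give, about 7–9 and 17–19 (about 14 new mothers in the smallest villages), naming the assumptions. If the survey has been done, give the actual numbers per group instead; sections 2 (Introduction) and 2.1.4 are partly in the past tense, so this may be the case. The cost is one sentence.

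If fieldwork has not started, the alternative is to draw the same 26 mothers on non-overlapping bands that match the analysis groups: up to 13 at random from 26–36 months, or all if there are fewer, and the rest at random from 6–25 months. This has two small costs. The full capture of the 18–24-month band is lost, and villages below about 350 people would still fall short of 12 in the older group, so the text should say so.
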